### Governance

Decisions relating to study design and protocol, ethics requirements, and research dissemination have been and will continue to be made by the research investigator group who meets monthly. Overall, 3 working groups will be established, comprising research investigators and key stakeholders to oversee and advise on development, implementation, and evaluation of the (1) merchandising strategy, (2) customer intercept survey, and (3) qualitative study to identify the policy supports for scale-up of health-enabling policy action in stores. A communication and research dissemination strategy approved by the research investigator group will govern internal and external stakeholder communication. This includes feedback of study findings and lessons learned at the end of the study to the ALPA and Island and Cape boards and participating communities.

### Study Outcomes

#### Primary Outcome

The primary outcome is difference in free sugars (g/MJ) from baseline in intervention versus control stores derived from store sales data. Free sugars contributed 26% of total energy purchased from 20 community stores, more than double the World Health Organization recommendation of less than 10% of total energy intake [36]. Our outcome measures were informed by modeling the estimated impact of the intervention on both target product categories and nutrients, using 49 continuous weeks of nonintervention store sales data collected from 20 remote Indigenous communities who participated in the SHOP@RIC study.

#### Secondary Outcomes

We will assess the impact on store revenue as a secondary outcome. This measure was considered by ALPA as important in determining the impact on retail performance. A necessary outcome for ALPA is that revenue is maintained throughout the intervention. Retail measures useful in evaluating specific merchandising effects on business operations will be examined where data are available, including number of products purchased per transaction (basket size), number of unique transactions, and category share of store sales. We will also collect data on intervention costs, including costs associated with strategy material production, implementation, and evaluation.

Our use of store sales data captures all foods and drinks sold, enabling an assessment of total nutritional quality of purchases as well as exploring impact on specific product types. We will examine the impact on purchases of targeted discretionary products (table sugar, sugar-sweetened beverages, sweet biscuits, and confectionery), total discretionary products, and nontargeted products (eg, water, diet drinks, fruit, and vegetables). We will examine the impact on the nutritional content of all food and drinks sold, including total energy, energy density, and nutrient density.

### Implementation Evaluation

#### Merchandising Checklist

We will assess intervention implementation using a Merchandising Checklist and the Store Environment tool (Store Scout App). The Merchandising Checklist will capture the intervention activities. Store managers from control and intervention stores will be requested fortnightly during the 12-week intervention period to respond to a brief checklist of intervention components delivered by a member of the research team via phone, and they will be requested to provide photos of premium locations (hot spots for product displays, such as high traffic areas, defined for each store following baseline data collection) to verify degree of compliance with intervention components. Store managers will be asked to comment on observations about community-level incidents that they perceive may affect sales (eg, weather events or festivals). They will also be asked questions related to their perceptions of intervention implementation and effectiveness.

#### Store Environment Tool (Store Scout App)

Store Scout App (developed and piloted by our team in 2016 in 6 remote stores) assesses the overall store as a consumer environment (ie, the retail choice architecture), through measures of stocking and merchandising of 7 categories of food and drinks (including fruit and vegetables, drinks, snacks, meals and convenience food, breads and cereals, dairy products and eggs, and meat and seafood). We will train government and Aboriginal Community-Controlled Organization employed public health nutritionists to conduct assessments in control and intervention stores. The tool will be completed at the end of the baseline, intervention, and postintervention periods.

### Customer Intercept Survey Substudy

In the final 2 weeks of the intervention, we will conduct customer intercept surveys (1080 unique customers; 45 per store) from control and intervention stores to identify the following:

Differences among customers in discretionary food and drink purchasing in intervention and control communities.Customer characteristics that predict discretionary product purchases.Proportion of customers who regularly purchase food and drinks from other food outlets in or outside of the community.

Using a structured close-ended question survey in electronic format (iSurvey) with standardized scripts, trained surveyors with support from store staff will interview customers after they complete their purchase. Surveyors will be scheduled to survey customers at store front (postshop) over a period of 6 hours (3×2 hour sessions over the course of the day) per day for up to 3 days, to capture a broad spectrum of customers and shopping purpose, planned or unplanned, each subject to different levels of impulse shopping propensity. We consulted with ALPA to ensure this is feasible on the basis of number of transactions per day. We anticipate surveys to take 5 to 10 min per customer.

Upon exiting the store, customers will be invited to provide their receipt (a photograph of the receipt will be recorded) and respond to a short-item questionnaire to gather information on characteristics of the customer (age range, gender, shopping alone versus with child or others, and impulse shopping propensity). Data on payment method (eg, cash or card) and food shopping frequency at other retail outlets will also be collected.

### Data Collection

The data source for the primary and secondary outcome analysis will be weekly sales reports generated by ALPA for each store for the entirety of the study and sent electronically to the research team. These data will include product identifier (stock keeping unit or barcode), product description, quantity sold, and dollar value. Store products will be linked to nutrient data using a database that we have developed specifically for this purpose, which is mostly derived from the Australian Food, Supplement, and Nutrient Database [37], with discretionary food flagged from the Discretionary Food List developed by the Australian Bureau of Statistics [38]. We will use built-in, reliable data checking processes that we have used over the last decade in our research to assess and quantify the nutritional impact of sales.

### Analyses

#### Effect of Intervention

Longitudinal data analysis models will be used on fortnightly store sales data aggregated from weekly sales. This will enable the effect of the intervention to be expressed as a relative change. Analyzing fortnightly data reduces variation because of income cycles, as observed in our previous analyses with sales data [6]. All models will include random effects for the stores and fixed effects for fortnight and intervention. Within-store residuals will be assumed to have an autoregressive structure of order 1. We will report effect sizes (and 95% CI) together with the associated *P* values.

Descriptive statistics will be used to describe contextual data. To assess implementation fidelity (as described in the implementation evaluation), a dichotomous variable of high or low fidelity will be derived from the repeat measures collected throughout the study in intervention and control stores using the Merchandising Checklist. Contextual and qualitative data will be analyzed to determine factors influencing implementation.

A store environment global score will be derived from use of the Store Scout App and compared across the 3 time periods. We will assess the degree to which the intervention has impacted the consumer environment and been sustained at 24 weeks postintervention in control and intervention stores.

Analyses will be conducted according to the intention to treat principle applied at store level; sensitivity analyses will be conducted looking at the stores’ implementation fidelity. Statistical analyses will be performed using Stata version 15.

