### Design

We will use a community-level pragmatic randomized parallel group, 2-arm, superiority trial with a 1:1 allocation ratio design and a baseline, 12-week intervention period and 24-week postintervention period to assess the effect of the intervention on customer purchasing and store business performance measured objectively through store sales data (Figure 1). We will use a customer intercept survey to address our second aim of determining the characteristics of customers associated with discretionary product purchasing. An in-depth implementation evaluation will assess implementation fidelity (ie, intervention compliance) using a Merchandising Checklist administered fortnightly by phone with store managers and accompanying in-store photographs captured by store managers. A Store Environment Tool “Store Scout” (developed by Menzies School of Health Research) will be used to assess changes to the retail choice architecture and contextualize the results.

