### Eligibility and Recruitment

#### Recruitment of Stores

This research will be conducted in partnership with ALPA who, at the time of designing the study, managed 25 stores in 24 communities. The ALPA stores comprise 3 corporation types, as these are as follows: company owned stores (6 in Queensland), stores managed on behalf of Aboriginal store owners (12 in NT and 1 in Queensland), and member stores where community residents are the shareholders (6 in NT). Overall, 12 of these stores operate in communities where there is more than 1 store. All stores managed by ALPA will be eligible. Using stores managed by a single store association will help ensure uniform and high-level implementation fidelity. In the 1 community where there are 2 ALPA stores, both stores will be allocated together to intervention or control during randomization.

The recruitment process will commence with the study being first presented and discussed with the ALPA and the Island and Cape boards. These boards are able to give consent for the ALPA and Island and Cape owned stores. On approval from the ALPA board, contact will then be made with each of the stores in NT with a management agreement with ALPA and a meeting arranged with the respective store boards. A study story will be used to facilitate a face-to-face discussion with store board directors. This will be facilitated by ALPA personnel alone or together with a member or members of the research team. Local authority groups in each of the communities will be informed of the study via a letter describing the study purpose and indicating that the community store board will be invited to participate.

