### Implementation

The ALPA General Manager of Retail Services and ALPA Nutritionist, who are both study investigators, will use a store task list, and they will use a drinks fridge planogram (physical layout diagram) developed by ALPA with input of the study investigators on proportion of unhealthier to healthier drinks, to communicate to store managers and their area managers about what is required. The task list will be developed on the basis of merchandising practice observed and photographed for each intervention store at baseline, specifically tailored on the basis of each store’s unique premium high traffic areas such as counter, front- and end-of-aisles, and store entrance. The task lists will indicate the maximum number of shelf facings for sugar, sugar-sweetened beverages, sweet biscuits, and confectionery product categories, with a list of substitutable core food products to fill the space opened. Substitutable core products will be identified with ALPA and indicated to store managers in a 2-page reference guide. Fidelity to no price reductions on targeted products will be maintained from baseline, with no changes during the intervention period, via ALPA’s standard pricing procedures. ALPA will lead the implementation of the intervention and will support the training of its store staff in implementation procedures for each of the intervention stores at start-up. The store will be relayed (ie, implementation of strategy) in consultation with store managers by members of the research team with an ALPA area manager or the ALPA nutritionist with an ALPA area manager. Store managers will use photographs of the newly relayed store to communicate stocking procedures to store staff for strategy maintenance. Thereafter, store managers will be responsible for maintaining the intervention with the support of their area managers. We expect some local adaptation of the intervention because of heterogeneity in the physical design of each store and input on implementation from store directors, but ALPA will aim for standardization of the intervention delivery across stores. Strict monitoring of intervention compliance will be conducted by the research team (see the Implementation Evaluation section below). Any nonadherence identified through monitoring will be communicated immediately to the responsible store manager to correct.

**Table 1 table1:** Intervention components.

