## Results

As of August 2018, 20 stores consented to participate and were randomized to receive the intervention or continue usual practice. The 12-week strategy ended in December 2018. The 24-week postintervention follow-up will occur in May 2019. Results are expected for 2019.

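### The primary model names no store-by-period term, so its confidence interval can be too narrow if stores shift or respond differently between periods

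*Protocol article*

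**What the plan says.** The protocol article, under Effect of Intervention, sets the unit of data: "Longitudinal data analysis models will be used on fortnightly store sales data aggregated from weekly sales". That gives 6 fortnights in the 12-week intervention and 12 in the 24-week follow-up; the length of the baseline is not given. The same paragraph fixes the model: "All models will include random effects for the stores and fixed effects for fortnight and intervention". It then adds: "Within-store residuals will be assumed to have an autoregressive structure of order 1". No term lets a store's level move from one study period to the next.

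The Design section describes a "superiority trial with a 1:1 allocation ratio design", and Results reports that "20 stores consented to participate and were randomized to receive the intervention or continue usual practice". I read this as 10 stores per arm.

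Elsewhere the article anticipates that stores will not all change alike:
- Implementation: "We expect some local adaptation of the intervention because of heterogeneity in the physical design of each store".
- Table 1, item 6, limits large soft-drink units only where there is no competitor outside the ALPA group. Recruitment of Stores says 12 of the 25 stores are in communities with more than one store.
- Merchandising Checklist asks managers about local incidents that may affect sales.
- Effect of Intervention plans to classify stores as high or low fidelity and to run sensitivity analyses on this.

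**The concern.** The effect is a comparison between arms of how much each store changed from baseline. A store random intercept drops out of that change. What remains in the stated structure is AR(1) noise, whose correlation fades with each fortnight. A shift that lasts the whole intervention period, such as a new local competitor or a sustained difference in delivery, does not fade. The model can absorb it only in part, by raising its estimate of the AR(1) correlation. It then credits the repeated fortnights with more independent information than they hold.

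The standard error of the primary effect, and so the interval and P value, would be too small. The trial has 20 stores, and longer series per store cannot make up for variation between stores in how they change.

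**Working it through.** **1. The article's own figure.** Sample Size gives a 95% interval of ±3.6% for two random groups of 10 stores, and about 90% power for a 6% reduction.
- SE = 3.6/1.96 = 1.837 percentage points.
- Power = Φ(6/1.837 − 1.96) = Φ(1.307) = 0.904. The stated 90% reproduces.
- Implied SD of a single store's change = 1.837 × √(10/2) = 4.107 points.

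**2. Simulation of the stated model, read as random intercepts.** There were 20 stores (10 per arm), 6 intervention fortnights, an assumed 6 baseline fortnights, no true effect, and 1000 runs per setting. Each store had an intercept, an independent effect for each period (variance τ²) and AR(1) residuals (variance σ², correlation ρ). The total variance of store change was held at 4.107², so drift is part of the article's precision and not added to it:
- τ² = share × 4.107²/2. At a 25% share τ = √(0.25 × 16.87/2) = 1.45; at 50% it is 2.05.
- σ² takes the remaining (1 − share) × 4.107².

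Each data set was fitted by REML with a store intercept, AR(1) residuals, and fixed fortnight, arm and intervention terms. Coverage is for estimate ± 1.96 SE.

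| Assumed share | ρ | Coverage | Model SE / true SE |
|---|---|---|---|
| 0% | 0.2 | 0.954 | 1.00 |
| 0% | 0.5 | 0.940 | 0.98 |
| 25% | 0.2 | 0.944 | 0.92 |
| 25% | 0.5 | 0.914 | 0.87 |
| 50% | 0.2 | 0.876 | 0.78 |
| 50% | 0.5 | 0.830 | 0.70 |

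Simulation error is about 0.007 at 0.95 (√(0.95 × 0.05/1000)) and 0.011 at 0.85. At a 75% share coverage was 0.74–0.78. Adding 12 follow-up fortnights, or dropping the arm term, gave 0.870 and 0.880 at a 50% share with ρ = 0.3.

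At a 50% share the model would report an average half-width of about 0.70 × 3.6 = 2.5 to 0.78 × 3.6 = 2.8 points, where 3.6 is correct. A t reference with 18 degrees of freedom raises coverage only to 0.85–0.90, so the missing variance component is the main problem.

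**3. Differences in effect alone.** Suppose stores drift alike but the effect varies with SD s across the 10 intervention stores. The true SE is then √(1.837² + s²/10). With s assumed at 3 to 5 points:
- s = 3: √(3.374 + 0.9) = 2.067; half-width 4.05; power for a mean effect of 6% = Φ(6/2.067 − 1.96) = 0.83.
- s = 5: √(3.374 + 2.5) = 2.424; half-width 4.75; power for 6% = Φ(6/2.424 − 1.96) = 0.70, and for 8% = Φ(8/2.424 − 1.96) = 0.91.

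In a separate simulation (maximum likelihood, z intervals, ρ = 0.3), the intercept-plus-AR(1) interval covered the average effect 91% to 89% of the time over this range. With no variation the same set-up had 6.6% type I error, which is 93.4% coverage. When store-by-period SDs of 2–4% were added instead, its type I error was 10.7–17.4%, whereas a t test on store-level changes kept 4.0–5.7%.

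**The case against.** The strongest reply is that nothing in the article shows such variation to be present, and without it the stated model performs as it should (coverage 0.94–0.95). That stands. A reader might infer that the intervals will be too narrow; the documents support only that they can be.

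The wording also leaves room. Store random effects, in the plural, do not exclude a random slope or period effect, and the customer substudy says random intercept when it means one. A condensed article may simply not spell this out. This is a fair caution against saying the model allows only intercepts. Even so, the covariance is stated concretely, and a period term is not part of it.

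Other tempting readings do not hold:
- **Twenty stores are too few in themselves.** A t(18) multiplier in place of 1.96 widens the interval by 2.101/1.960 = 1.07. The degrees-of-freedom method is commonly left to an analysis plan that is not shown, so its absence is no finding.
- **Community clustering is a material omission.** ALPA "managed 25 stores in 24 communities", so at most one pair exists, and "both stores will be allocated together to intervention or control during randomization". Even with perfect correlation within the pair, the SE rises by √((0.12 + 0.10)/0.20) = 1.049, about 5%; at correlations of 0.2 and 0.5 it rises by 1.0% and 2.5%. The article does not say that both stores are among the 20.
- **Varying fidelity inflates the test of no effect.** If the intervention does nothing in any store, there is no effect to vary. Such differences bear on the interval for the average effect. Only differing drift inflates that test.
- **The ±3.6% ignores store drift.** It comes from real sales in 20 stores, and the model behind it is not named, so this cannot be shown. What it must lack is variation in the effect of an intervention that was not being delivered.

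**Conclusion.** The point holds in conditional form. Read as store intercepts plus AR(1) residuals, the primary model can give too narrow an interval if stores drift differently between periods or respond differently, and the article gives its own reasons to expect differing responses. The loss is small if store-by-period variation is a quarter of the variance of store change, and serious if it is half: the SE is then 22–30% too small. If there is none, nothing is lost.

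These sizes rest on assumed variance shares, ρ between 0.2 and 0.5, 6 baseline fortnights and 10 stores per arm. The planned precision and power are a best case only in that they contain no between-store variation in effect. At the article's anticipated 8–9% effect, power stays at about 0.91 or above over the range assumed here.

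**What to change.** State the random part of the primary model in full: a store intercept, store-specific random coefficients for the intervention and post-intervention periods, and AR(1) residuals. If the store random effects were already meant to include these, saying so is enough.

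Add a prespecified check: compute the change in mean log g/MJ from baseline for each randomized unit, and compare arms by a permutation or t test. Treat the two co-allocated stores as one unit if both are enrolled.

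Beside the ±3.6% and the 90% power, note that they include no between-store variation in the intervention effect.

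The cost is analysis wording, a little more work and somewhat wider intervals. Design and data collection are unaffected.

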#### Customer-Level Response (Substudy)

Percent discretionary product to total food and beverage dollars (dependent variable) will be calculated for each receipt collected during the Customer Intercept survey. Associations between the dependent variable and dichotomous variables indicating exposure or no exposure to the intervention will be estimated using mixed-effects linear models. Effect of the intervention will be expressed in terms of percent difference relative to the control group adjusting for baseline differences in merchandising. Mixed models will include a random intercept for community to account for within community correlation (clustering effect). As this is a convenience sample of customers, the potential confounding effect of baseline exposure to merchandising of targeted products, age range, and gender will be explored by including these factors in the models. Store Scout will be conducted at baseline in control and intervention communities to provide a proxy of merchandising exposure at baseline. Multivariable linear mixed models (with random intercept for community) will be conducted to identify customer characteristics (eg, payment type) associated with purchase choice.

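### The customer survey contrast adjusts at store level only for a baseline merchandising proxy, although each community's baseline discretionary dollar share can be derived from sales data already held

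*Protocol article*

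**What the plan says.** All references are to the protocol article.

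- **Timing.** The section on the intercept survey fixes when receipts are gathered: "In the final 2 weeks of the intervention, we will conduct customer intercept surveys (1080 unique customers; 45 per store) from control and intervention stores". No baseline survey wave is described.
- **Outcome.** Under Analyses, the part on customer-level response defines the dependent variable as follows: "Percent discretionary product to total food and beverage dollars (dependent variable) will be calculated for each receipt collected during the Customer Intercept survey".
- **Adjustment.** The same section expresses the intervention effect relative to control, "adjusting for baseline differences in merchandising", and names the measure: "Store Scout will be conducted at baseline in control and intervention communities to provide a proxy of merchandising exposure at baseline". It also lists possible confounders to examine: "baseline exposure to merchandising of targeted products, age range, and gender will be explored by including these factors in the models". The models carry a random intercept for community.
- **Data already available.** Data Collection describes "weekly sales reports generated by ALPA for each store for the entirety of the study" and states: "These data will include product identifier (stock keeping unit or barcode), product description, quantity sold, and dollar value". Products are linked to a nutrient database in which discretionary foods are flagged. The abstract's Methods paragraph confirms that sales data are collected at baseline.
- **Planned power.** Sample Size, Customer Response: ICC 0.01, 45 customers in each of 24 communities, 1080 customers, design effect 1.4, and 80% power for 50% versus 42% at alpha .05. The Results section reports that 20 stores were randomized.

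**The concern.** The arm comparison on receipts is made after intervention only. Communities may differ in discretionary spending before the intervention starts, and with about 20 clusters chance can leave the arms unequal. The article accepts that baseline differences call for adjustment, but it chooses a measure of the store environment. Store Scout scores stocking and merchandising across seven broad categories, including meat and seafood, dairy products and eggs, and breads and cereals. It does not measure what people buy.

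The sales reports measure the outcome's own construct, at the level where allocation took place and before the intervention. A covariate of that kind would ordinarily be expected to explain more of the between-community variance than an environment score. At stake is precision in a contrast that the article sets up and powers, and protection of that contrast from a chance imbalance.

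**Working it through.** **Inputs.** From the article: ICC 0.01; m = 45 per community; k = 24 communities planned and 20 stores randomized; difference 8 points (50% versus 42%); alpha 0.05; 1:1 allocation. Assumed: two-sided test; 20 stores treated as 20 communities; SD of 40 percentage points (see step 1); and R², the fraction of between-community variance in the receipt outcome that the baseline sales share explains. The article gives no value for R², so a range of 25% to 80% is shown.

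**1. The article's own figure.** Power = Φ(Δ/SE − 1.96), with SE = SD × √(2 × DE / n per arm) and n = 540 per arm.

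- DE 1.4: SE = 40 × √(2.8/540) = 2.88; 8/2.88 = 2.78; power 79.3%.
- DE 1 + 44 × 0.01 = 1.44: SE = 2.92; power 78.2%.

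The stated 80% is reproduced and is not in dispute. It needs an SD of 40 points. Read as 40% of 50, the SD would be 20 points and power 99.98%.

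**2. How much variance a community-level covariate can reach.** The variance of a community mean has two parts:

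- between communities: 0.01 × 1600 = 16 (SD 4 points);
- within communities: 0.99 × 1600 / 45 = 35.2.

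The between part is 16/51.2 = 31%. The other 69% is receipt-to-receipt variation that this covariate does not touch.

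**3. Chance imbalance between arms in true community means.** SD = 4 × √(4/k).

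- k = 20: 1.8 points; probability of an imbalance above 2 points, about 26%.
- k = 24: 1.6 points; about 22%.

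The target effect is 8 points.

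**4. Effect of adjusting.** SE = √[(4/k) × (16 × (1 − R²) + 35.2)]. The t column uses k − 2 degrees of freedom unadjusted and k − 3 adjusted. For k = 20 (900 customers):

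| R² | SE (points) | 8/SE | Power, normal | Power, t |
|---|---|---|---|---|
| 0 (unadjusted) | 3.20 | 2.50 | 70.5% | 65.7% |
| 25% | 3.07 | 2.60 | 74.0% | 69.0% |
| 50% | 2.94 | 2.72 | 77.7% | 72.8% |
| 80% | 2.77 | 2.89 | 82.3% | 77.7% |

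For the planned k = 24, normal approximation, power is 78.2% unadjusted and 81.4%, 84.7% and 88.5% at the same three values.

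**5. Comparison with the clusters lost.** Going from 24 to 20 clusters costs 78.2 − 70.5 = 7.7 points of power. Adjustment at 20 clusters returns 3.5, 7.2 or 11.8 points. At R² = 25% that is under half of the loss, at 50% nearly all of it, and at 80% more than all of it.

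**6. Sensitivity to the ICC.** If the ICC were 0.02 (assumed), with 20 clusters and the normal approximation, power would be 59.0% unadjusted and 64.5%, 70.8% or 79.5% adjusted.

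**The case against.** The case against is substantial, and parts of it stand.

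- **The planned analysis is valid.** A reader might infer that baseline differences bias the contrast. The article does not support that: allocation is random, so differences balance in expectation, and the community random intercept carries chance differences into the standard error. This objection stands; what is lost is precision.
- **Merchandising is not the only covariate.** A reader might infer that nothing else is adjusted for. Age range and gender are also explored. That stands, although neither is a baseline measure of purchasing, so Store Scout remains the only baseline store-level adjuster named.
- **Between-community variance is not the main limit.** At ICC 0.01 it is 31% of the variance of a community mean. That stands, and it caps the gain.
- **The gain depends on an assumption.** The sales share is weighted by dollars over all transactions in an earlier period; the outcome is a per-receipt percentage from a convenience sample. The correlation will be below 1, and a small R² is possible: at 10%, power moves only from 70.5% to 71.9%. That stands.
- **A covariate list can be left to the analysis plan.** This stands only in part. The article recognizes the need for baseline adjustment and names the adjuster, so the point challenges a stated choice, not an omitted detail.
- **Store-level discretionary sales are already analyzed longitudinally as a secondary outcome.** True, but that analysis does not improve the receipt-level contrast, which has its own stated aim and sample size.

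**Conclusion.** The point holds as a matter of efficiency. The article names a proxy as its baseline store-level adjuster for the survey contrast, while a more direct baseline for the outcome can be derived from data the trial already receives.

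The size is modest. At ICC 0.01, SD 40 points and 20 x 45 customers, the gain is about 3 to 12 points of power for R² between 25% and 80%, with either normal or t critical values. It would be larger at a higher ICC. R² is an assumption throughout. The comparison is with no community-level covariate, so whatever Store Scout itself explains would reduce the net gain; the article gives no figure for that.

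A reader might also infer that this weakens the trial's main result. It does not: the primary outcome comes from store sales with baseline data, and only the substudy's intervention contrast is affected.

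**What to change.** In the receipt-level mixed model for the intervention contrast, prespecify as a covariate each community's baseline-period discretionary share of food and beverage dollars, computed from the ALPA sales reports with the discretionary flag already planned. Where one community has two participating stores, pool their sales. State the baseline window. Report the Store Scout-adjusted model as secondary, and keep age range and gender as planned.

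The cost is one community-level degree of freedom (17 instead of 18 with 20 clusters), which the t column above already charges, and the work of deriving one variable. No new data collection is needed. The covariate will correlate imperfectly with the per-receipt outcome, so the gain may fall at the low end of the range.
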